## Data collection and management

### Plans for assessment and collection of outcomes {18a}

Personal data concerning the subjects is protected in accordance with the Data Protection Regulation (GDPR—General Data Protection Regulation) and the Data Protection Act as well as the Health Act. Documentation for the research project is submitted to the Capital Region of Denmark’s Research List.

Data is stored and analyzed on a secure network drive with secure access only to staff directly involved in the trial conduct in pseudo-anonymized form in accordance with guidelines specified by the Danish Data Protection Agency and the GDPR. Standard blood samples for immediate analysis when monitoring treatment are labeled with subjects’ names and CPR numbers, and blood sample responses will appear in the patient record. Other research blood samples for the research biobank are pseudonymized with identification labels.

Research results belong to the trial site, and results are not handed out. The protocol is performed according to the Declaration of Helsinki II, and trial participants may withdraw from the trial at any time without further explanation.

### Plans to promote participant retention and complete follow-up {18b}

According to the existing standard of care (SOC), follow-up after mesenteric stenting at Rigshospitalet is an outpatient visit, including clinical examination and DUS at 6 weeks and 12 months postoperatively. According to guidelines, FU after stenting of mesenteric arteries includes clinical examination and DUS at 1 month, 6 months, 12 months, and annually thereafter [9].

In this trial, annual FU outpatient visits until the fifth postoperative year, including DUS, are planned. In addition, a CTA at 12 months has been added to validate the DUS findings. In summary, because of the present study, the participating patient will receive care in better adherence to internationally accepted guidelines using of CS instead of BMS (half of the patients) and yearly FU for 5 years instead of 1 year FU only (all patients).

If a patient chooses to not participate in the trial after randomization, patients will receive care according to current SOC.

### Data management {19}

Personal data concerning the subjects is protected in accordance with the Data Protection Regulation (GDPR—General Data Protection Regulation) and the Data Protection Act as well as the Health Act. Documentation for the research project is submitted to the Capital Region of Denmark’s Research List. The project responsible physician and project nurse are responsible for data management and electronic data entry of CRF in REDCap. Any paper-based CRF are stored in a secure place in the trial office.

### Confidentiality {27}

Data is stored and analyzed on a computer in pseudo-anonymized form in accordance with guidelines specified by the Danish Data Protection Agency and the GDPR. Control blood samples for immediate analysis when monitoring treatment are labeled with subjects’ names and CPR numbers, and blood sample responses will appear in the patient record. Other research blood samples for the research biobank are pseudonymized with identification labels. Data and participant details are stored on Research Electronic Data Capture (REDCap) and will only be accessible by trial members. Any paper-based CRF, including signed informed consent, are stored securely in the trial office.

### Plans for collection, laboratory evaluation, and storage of biological specimens for genetic or molecular analysis in this trial/future use {33}

The blood sample and tissue residues will constitute a research biobank located at Rigshospitalet, which will be stored for the project’s duration until the final analysis plan is available in collaboration with relevant partners at Rigshospitalet. The COMESS research biobank will be discontinued on 01–06-2031. After completing the study, the remaining material is transferred for storage in a biobank for future research, which is reported to the Capital Region’s Knowledge Centre for Data Processing and follows the Data Protection Ordinance and the Data Protection Act. The biobank for future research will be established to carry out future supplementary studies and utilize any technological development after renewed approval from relevant authorities. The participants in the experiment give separate consent for the storage of residual material in a biobank for future research.

## Statistical methods

### Statistical methods for primary and secondary outcomes {20a}

Outcomes are analyzed on intention to treat basis and secondarily per protocol. Primary outcomes will be analyzed by *t*-test and overall survival analysis, to estimate the patency at 12 months.

Secondary endpoints will be analyzed by survival analysis techniques, such as Kaplan–Meier curve and log-rank tests. ANOVA repeated measures will be used to estimate comparison QoL between the two groups, and secondary stent patency. Log-rank test will be used to compare the survival rates between groups. Sensitivity and specificity of CTA and US will be analyzed with a logistic regression and receiver operator curves (ROC) analysis.

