### Intervention description {11a}

The procedure will take place in an angiography suite under local anesthesia. Access will primarily be gained from the femoral artery using a 6–8 Fr sheath. An alternate vascular access route, primarily the brachial artery, can be chosen at the operator’s discretion. After the target lesion has been crossed with a 0.035 guidewire, a pressure gradient across the lesion will be determined using a mean pressure gradient > 15 mmHg to define significant lesions [5]. In the case of an occlusion or near occlusion of the SMA, intra-arterial pressure measurement is omitted as it is not technically measurable. The lesion is then treated based on the pre- and intraoperative imaging. Patients with a significant lesion will then be randomized to either BMS or CS treatment. The treating physician will choose the appropriate stent length and diameter based on pre- and intraoperative imaging. The stent should cover the entire primary lesion and protrude 3–5 mm into the aorta to achieve total lesion coverage. Bare metal stent extensions (either balloon expandable or self-expandable) can be placed at the discretion of the operator to allow optimal conformity to the target vessel or minimize the risk of target vessel dissections. The stent is dilated to minimum the nominal pressure given by the manufacturer to achieve nominal stent size.

The treatment result is evaluated by standard angiography in two planes and measuring the pressure gradient across the stented segment. Two plane angiography can be substituted by on-table beam CT or angiography in one plane combined with a single X-ray in two planes to determine stent compression. Less than 30% residual stenosis and/or mean pressure gradient < 15 mmHg is considered a treatment success.

All patients will have the balloon catheter used for ballooning the stenosis/occlusion collected. Residual material from the PTA balloon and blood samples from the angioplasty catheter (< 50 ml blood) will be collected during the procedure and stored at − 80 °C in a research biobank until analysis. Peripheral blood samples (< 50 ml blood in total) will be collected in connection with PTA treatment, as well as during the yearly outpatient visits (< 50 ml) to analyze circulating blood markers.

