## Outcomes {12}

### Primary endpoint

Primary stent patency at 1 year (< 50% stenosis)

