### Sample size {14}

In the only study investigating CS vs BMS in CMI [10], a retrospective non-randomized study of 225 patients, patients treated by CS had freedom from restenosis of 92% ± 6% compared to BMS with freedom restenosis of 53% ± 4% [10]. This study suffered several limitations that must be considered for a sample size estimation in the present RCT: the velocity cut-off used may overestimate high-grade restenosis, the follow-up was significantly longer in the BMS group, and differences in time-dependent outcomes including restenosis must be expected. In addition, a general underreporting of outcomes in both the BMS and the CS arm must be expected in a retrospective study. Therefore, the expected restenosis rates were adjusted to 85% and 60%.

Using dichotomous endpoints (restenosis: Y/N), a two independent sample study, alpha = 0.05, beta = 0.2, and power = 0.8, sample size was estimated to 49 patients in each group (total = 98). With 120 CMI/AoCMI patients treated yearly in Copenhagen, an estimated inclusion rate of 80% and 20% dropout, a total of 77 CMI patients will be randomized yearly (app 6 pts/month)—and 98 patients are expected included within 18–24 months.

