### Recruitment {15}

Patients are discussed in a multidisciplinary team (MDT) at Copenhagen University Hospital (Rigshospitalet) in Denmark, including vascular surgeons and interventional radiologists after the referring physician has ruled out other gastrointestinal causes. If a consensus decision of CMI or AoCMI is reached and the diagnostic workup and clinical findings support endovascular treatment, the patient is invited to participate in the study.

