## Assignment of interventions: allocation

### Sequence generation {16a}

The process of randomization is done in Research Electronic Data Capture (REDCap). Randomization will be in block sequence to get equal patient allocation in the two treatment arms in REDCap, a third party electronic dataset system, and accessible only to the physician/research nurse/coordinator performing the randomization. Only the treating team will know the allocation (CS vs BMS).

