### Methods for additional analyses (e.g., subgroup analyses) {20b}

Not applicable. Subgroup analysis or any other additional analysis is not planned for this trial, as it will likely result in an insufficient sample size.

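### The stated patency and quality-of-life comparisons name no baseline covariate, although useful ones are known before allocation: a cheap, optional efficiency gain, not an error

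*Protocol article*

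**What the plan says.** The primary endpoint is binary: "Primary stent patency at 1 year (< 50% stenosis"). Section {20a} states "Outcomes are analyzed on intention to treat basis and secondarily per protocol. Primary outcomes will be analyzed by" a t-test and survival analysis, and names no covariate. The same section compares QoL between arms by repeated-measures ANOVA, again without a covariate. Section {20c} mentions mixed models, but only as the way to handle missing data.

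The trial design section {8} gives 1:1 block randomisation. Sequence generation {16a} adds: "Randomization will be in block sequence to get equal patient allocation in the two treatment arms in REDCap". Neither names a stratification factor. Section {20b} says: "Subgroup analysis or any other additional analysis is not planned for this trial", and gives insufficient sample size as the reason.

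Three kinds of baseline information exist before allocation:

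- **Presentation.** The multidisciplinary team settles it before the patient is invited (Recruitment {15}): "If a consensus decision of CMI or AoCMI is reached".
- **State of the SMA.** The intervention description {11a} says: "In the case of an occlusion or near occlusion of the SMA, intra-arterial pressure measurement is omitted". This comes before randomisation, which takes place after the lesion has been crossed (Implementation {16c}).
- **QoL.** Table 1 schedules EQ-5D-5L and SF-36 at baseline.

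**The concern.** The trial pools CMI with AoCMI and stenosis with occlusion, in 49 patients per arm. Blocking equalises arm totals but not the mix of patients within them. If presentation or occlusion affects 12-month patency, adjusting for it would sharpen the stent comparison and take out the part of any chance imbalance that the factor explains, with no extra patients. The same holds for QoL, where a patient's baseline score usually tells much about later scores. What is at stake is some precision, and how easily the result can be defended if the arms happen to differ at baseline. The validity of the main test is not at stake.

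**Working it through.** **1. The plan's own figure.** Inputs from Sample size {14}: "alpha = 0.05, beta = 0.2, and power = 0.8, sample size was estimated to 49 patients in each group (total = 98"), and "Therefore, the expected restenosis rates were adjusted to 85% and 60"%. The label there says restenosis, but the figures derive from freedom from restenosis; the sample size is the same for the complements. Sidedness is not stated, and two-sided is assumed. With mean proportion 0.725 and pooled variance:

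n = [1.96 × √(2 × 0.725 × 0.275) + 0.8416 × √(0.85 × 0.15 + 0.60 × 0.40)]² / 0.25² = (1.2377 + 0.5102)² / 0.0625 = 48.9, so 49 per arm.

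The figure reproduces, with power 80.1%. It assumes an unadjusted comparison, so the planned power does not depend on adjustment.

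**2. Chance imbalance.** The article gives no prevalence for either factor, so a range is assumed. For two independent groups of 49, the chance that the arms differ by at least 10 percentage points in one binary factor is:

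| Prevalence | Chance |
|---|---|
| 20% | 25% |
| 30% | 32% |
| 40% | 35% |

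Fixing the total number with the factor gives figures that depend on whether that total is odd or even (at about 30%: 37.6% for 29 patients, 27.3% for 30). The binomial figures average over this.

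If the factor shifts patency by 20 points (assumed), a 10-point imbalance moves the estimated difference by 0.20 × 0.10 = 2 points, and a 20-point imbalance by 4 points, against a planned difference of 25.

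**3. Variance gain from one covariate.** Let q be the prevalence and r the patency difference it carries. The variance term is 0.85 × 0.15 + 0.60 × 0.40 = 0.3675 without adjustment, and 0.3675 − 2r²q(1−q) with it. For q = 0.3 and r = 0.20: 0.3675 − 2 × 0.04 × 0.21 = 0.3507, a ratio of 0.954. Unpooled Wald power goes from 82.3% to 84.0%. For q from 0.1 to 0.5:

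| r | Variance cut | Power after adjustment |
|---|---|---|
| 10 points | 0.5–1.4% | 82.5–82.8% |
| 20 points | 2.0–5.4% | 83.0–84.3% |
| 30 points | 4.4–12.2% | 84.0–86.9% |

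**4. Both covariates, simulated.** Marginal patency is 85% against 60%, with 49 per arm, and the assumed prevalences are 25% (AoCMI) and 30% (occlusion). Each factor has the same assumed odds ratio for loss of patency. The unadjusted pooled z-test has about 81% power throughout. The adjusted power is from a logistic likelihood-ratio test; the variance ratio is for the standardised risk difference.

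| Odds ratio | Adjusted power | Variance ratio |
|---|---|---|
| 1 | no gain | 1.016 |
| 2 | 82% | 0.972 |
| 3 | 84% | 0.931 |
| 4 | 86% | 0.895 |

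A separate simulation used linear regression with robust standard errors and prevalences of 20–30%. Power, unadjusted against adjusted, was 81.3% and 80.4% with no prognostic effect, 80.6% and 81.1% at 10 points per factor, and 81.0% and 84.0% at 20 points per factor. The overall range is therefore about -1 to +5 points.

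**5. Type I error.** It is 4.8–5.2% for the unadjusted test and for the linear adjusted test. The logistic likelihood-ratio test runs at about 5–6%, and a standardised difference with robust errors rejected 5.5% at odds ratios 3 and 4. Part of the upper end of the power gain in step 4 reflects this.

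**6. QoL.** With equal variances and correlation ρ between baseline and follow-up, the large-sample variance of ANCOVA is (1 − ρ²) times that of a follow-up score comparison and (1 + ρ)/2 times that of a change-score comparison. At an assumed ρ = 0.5 these are 1 − 0.25 = 0.75 and 1.5/2 = 0.75, so 25% lower than either.

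**The case against.** The strongest reply is that this is a preference. Randomisation makes the unadjusted estimate unbiased on average, its type I error already allows for chance imbalance, and the sample size was set for it. All of that stands. Covariate lists and stratification factors are also commonly left to the full protocol or analysis plan, neither of which is shown, so silence in an article does not prove absence.

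Four stronger readings are tempting, and the document does not support them:

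- **That precision is being lost.** This requires the factors to be prognostic for 12-month patency. No passage says so, and all prevalences and effect sizes above are assumed.
- **That the article itself treats presentation as prognostic.** Background {6a} defines AoCMI as AMI in patients with a history of CMI, and keeps AMI out of randomisation for its diversity and acute mortality. The same section randomises AoCMI, and it makes no statement about AoCMI and patency.
- **That a chance imbalance would invalidate the result.** A 10-point imbalance in a 20-point factor moves the estimate by about 2 points.
- **That section {20b} forbids adjustment.** It concerns additional analyses, with subgroups as its example. Its sample-size reason fits subgroup claims but not a covariate in a model that uses every patient. The wording is open to a broader reading, so it deserves clarifying.

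Two practical objections also stand. Occlusion appears in {11a} together with near occlusion and only to explain an omitted measurement, so the category needs defining. And few events are expected: 49 × 0.15 + 49 × 0.40 = about 27 losses of patency, about 7 of them with covered stents. For QoL, repeated-measures ANOVA may already include baseline as a time point; the article does not say.

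**Conclusion.** The point holds as an optional efficiency improvement. The methods as stated name no baseline covariate, and suitable ones are known before allocation. For patency the change in power is about -1 to +5 points under assumed prevalences of 25% and 30% and odds ratios from 1 to 4 per factor: a gain only if the factors are prognostic, and a variance cost of about 2% if they are not. Type I error with adjustment may be slightly above nominal, at about 5–6%. The QoL part is the clearer one, because ANCOVA never has larger large-sample variance than a follow-up or change-score comparison; the 25% figure rests on the assumed correlation of 0.5. The unadjusted intention-to-treat test remains valid and meets its stated 80% power.

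**What to change.** 1. In {20a}, analyse QoL with each patient's baseline score as a covariate, by ANCOVA or by a mixed model over the follow-up visits, in place of plain repeated-measures ANOVA.
2. Prespecify, before unblinded data are seen, a 12-month patency risk difference standardised for CMI/AoCMI and for SMA occlusion or near occlusion (yes/no), with small-sample robust or bootstrap standard errors. Show the unadjusted difference beside it. The timing matters because {21b} plans looks after one third and two thirds of inclusion.
3. Before using presentation as a covariate, reconcile the AoCMI passages. The abstract and Background {6a} randomise AoCMI, while {6a} also defines it as a form of AMI; the inclusion criteria name only CMI and the exclusion criteria list AMI.
4. State in {20b} that it concerns subgroup claims and not covariate adjustment.

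The cost is a few sentences and no patients. The downside is the variance cost of about 2% if neither factor matters, and the need to watch type I error with so few events.

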### Methods in analysis to handle protocol non-adherence and any statistical methods to handle missing data {20c}

Patients whom are not included in the trial for any reason are kept in a pseudonymized screening log to allow further analysis. Randomization of patients is performed on an intention to stent basis. Analysis of randomized patients will be done on an intention-to-treat analysis and per-protocol analysis will also be performed. To handle missing data, mixed models without imputation will be performed.

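### The primary yes/no patency endpoint is assigned a t-test and an overall survival analysis: neither is the two-proportion comparison the trial is sized on, and neither is named as deciding superiority

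*Protocol article*

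**What the plan says.** The protocol article defines the primary endpoint as "Primary stent patency at 1 year (< 50% stenosis"), one yes/no value per patient. The trial design section calls this a superiority trial with that endpoint.

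The sample size section treats it the same way: "Using dichotomous endpoints (restenosis: Y/N), a two independent sample study, alpha = 0.05, beta = 0.2, and power = 0.8". It then states that "sample size was estimated to 49 patients in each group (total = 98").

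The statistical methods section ({20a}) assigns the primary outcome a different pair of methods: "Primary outcomes will be analyzed by *t*-test and overall survival analysis, to estimate the patency at 12 months". It ranks the analysis sets, with intention to treat first and per protocol second, but it does not rank the two methods. The outcomes section lists overall survival as a secondary endpoint in its own right, apart from patency.

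The section on non-adherence and missing data ({20c}) adds: "To handle missing data, mixed models without imputation will be performed". It does not tie this to either primary method.

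**The concern.** A superiority claim needs one analysis, fixed in advance, whose result decides it. Here two are named. The first, a t-test, compares means. The second, read in the protocol's own vocabulary, compares deaths. Neither is the comparison of two proportions used to choose 49 per arm.

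Two methods without an order can give two answers, and the text does not say which one stands. This matters more because the steering committee, formed from the two clinical departments involved, is to look at efficacy after one third and two thirds of inclusion. If the deciding test is still open then, it could be settled by people who have seen outcome data.

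**Working it through.** **1. Reproduce the stated sample size.** Inputs from the sample size section: 85% and 60%, alpha 0.05, power 0.80. Sidedness is not stated; two-sided is taken. The section calls the two rates restenosis, but they are adjusted from freedom-from-restenosis figures of 92% and 53%, so they are read here as patency (85% CS, 60% BMS). The required number is the same for the complements.

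n = [1.960 × √(2 × 0.725 × 0.275) + 0.842 × √(0.85 × 0.15 + 0.60 × 0.40)]² / 0.25²
= (1.238 + 0.510)² / 0.0625 = 48.9, so **49 per arm**.

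This matches the stated figure, with 80.1% power. The design is therefore a two-sided comparison of two proportions without continuity correction (with the correction it would be 57; one-sided 39).

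**2. Does the t-test do harm in itself?** Exact enumeration of all binomial outcomes at 49 per arm:

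| Test | Power, 85% vs 60% | Type I error at common rates of 60%, 72.5%, 85% |
|---|---|---|
| t-test on 0/1 data | 80.9% | 5.0%, 5.0%, 4.7% |
| Chi-square | 80.9% | 5.0%, 5.0%, 5.5% |
| Fisher | 74.5% | 3.1%, 3.0%, 2.3% |

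The t-test is the wrong label for the data type, but it behaves almost like the chi-square test.

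**3. What if either of the two named methods may be declared the result?** Simulation with 8,000 runs per scenario, exponential times, 72.5% patency in both arms, and 12-month mortality of 5%, 10% and 15%. The mortality figures are assumptions; the document gives none.

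| Mortality | t-test alone | t-test or log-rank of patency | t-test or log-rank of death |
|---|---|---|---|
| 5% | 5.2% | 5.6% | 9.7% |
| 10% | 5.8% | 6.4% | 10.6% |
| 15% | 4.3% | 5.0% | 9.2% |

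The Monte Carlo standard error is √(0.05 × 0.95 / 8000) ≈ 0.24 points, so part of the spread down each column is noise. Within the same runs, adding the patency log-rank raises the error by 0.4 to 0.7 points (for example 5.56 − 5.15 = 0.41). Adding a death log-rank roughly doubles it, as expected for two independent tests (1 − 0.95² = 9.75%).

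**4. Can a comparison of deaths answer the question?** Under the planned 85% vs 60% patency effect with equal mortality in both arms, the death log-rank rejected in 4.5% to 5.2% of runs. It carries no information on patency.

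**5. If time to loss of patency was meant.** The follow-up section schedules a CTA at 12 months. Suppose a share f of failures is found only at that CTA and a share h of those scans is dated after month 12.0. A Kaplan-Meier difference read at exactly 12.0 then shows about 25 × (1 − f × h) points.

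- h = 0 (all scans dated by month 12): 25 points, no shift.
- f = 0.50, h = 0.50: 25 × 0.75 = 18.75 points (88.75% vs 70%).
- f = 0.75, h = 0.50: 25 × 0.625 = 15.6 points (90.6% vs 75%).

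Both f and h are assumptions, so this shows the sensitivity and does not forecast its size.

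**The case against.** The strongest reply is that the sentence gives its own purpose, estimating patency at 12 months, so a Kaplan-Meier analysis of patency is the natural reading and the word overall is a slip. On that reading, step 3 shows almost no inflation, and step 2 shows the t-test is harmless. Both points stand, and they limit the size of the finding. They do not remove it: the label would still be that of another endpoint, and two analyses would still be unranked. A separate analysis plan could settle the order, but a correct one would then contradict the published text.

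Several stronger readings are tempting, and the document does not support them:

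- *The primary endpoint is undefined.* It is defined; only its deciding analysis is not.
- *The primary analysis counts deaths.* That is the literal reading only, for the reason above.
- *The type I error doubles.* This needs someone to claim patency superiority from a comparison of deaths, and nothing in the protocol suggests that.
- *The survival estimate will shrink the contrast to 16 to 19 points.* No scan window is given, and the CTA is to be done before the scheduled follow-up visit. The effect also applies only to a curve read at exactly month 12; a log-rank test that includes later-dated events is not cut off there.
- *About 20 of 98 patients will be missing.* The 20% dropout is taken off before randomization: 120 × 0.80 × 0.80 = 76.8, given as 77 randomized yearly. No rate of missing 12-month scans is stated.
- *The missing-data rule amounts to complete cases.* Duplex ultrasound is scheduled at 6 weeks as well as, in the standard timeline, at 12 months, so a repeated-measures model could use patients without a 12-month scan. What can be said is that the rule is not linked to any named primary method.

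**Conclusion.** The concern holds as an error in what the article states. A binary endpoint, sized as two proportions, is assigned two other methods with no deciding one, and one of them bears the name of the secondary death endpoint.

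That conclusion rests on the text alone. The numerical cost is small on the likely reading: no loss of power from the t-test, and a type I error of about 5% to 6% if either the t-test or a patency log-rank could be claimed. It reaches 9% to 11% only on the literal reading with free choice between the tests. The type I error figures rest on assumed mortality of 5% to 15% and exponential times. Sensitivity to scan date is real for an estimate read at exactly 12 months, but its size cannot be fixed from the document.

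**What to change.** Reword the primary-outcome sentence in {20a} and the missing-data sentence in {20c}:

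- Name one primary analysis: the difference in the proportion with primary patency at 12 months (CS minus BMS), tested with a two-sided 0.05 chi-square test and reported with a 95% CI.
- Replace the overall survival analysis with a Kaplan-Meier and log-rank analysis of time to loss of primary patency, labelled supportive. Leave overall survival among the secondary endpoints.
- Drop the t-test.
- Align the missing-data sentence with the binary analysis and state how deaths before 12 months are counted. If imputation is chosen, it should not assign a patency state to patients who died unless that is the stated intention.

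The change should be made before any comparison of outcomes by arm. The sample size stays at 49 per arm with 80.1% power. The cost is rewording and slightly more analysis work; no new data are needed.

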### Follow-up

In this trial, patients will attend outpatient visits with clinical exams, blood samples, Duplex ultrasound (DUS), and quality of life (QoL) questionnaire at 6 weeks, 12 months, and then annually to 5 years postoperatively. CTA will be performed once at 12 months postoperatively, prior to the scheduled follow-up. In case of prohibitive traveling distance to the study site, the follow-up DUS at 1 year and beyond can be omitted from the protocol and replaced by CTA at investigators discretion. As the primary study endpoint is at 1 year, this alteration will not interfere with the conclusions. If there is suspicion of an in stent re-stenosis based on the clinical exam and DUS of the SMA (threshold 412 cm/s) [6], a patient will undergo a CTA. Following evaluation of CTA results and clinical examination, the patient may be offered additional treatment if indicated.

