### Secondary endpoint(s)—evaluated at 12 months and 5 years

Secondary stent patencyFreedom from stent re-stenosis (luminal diameter > 50%)Freedom from reinterventionOverall survivalIntervention free survivalFreedom from symptom recurrenceProteomics assay signal (balloon) and concentration of established biomarkers (blood samples)Quality of lifeSensitivity and specificity of CTA and US preoperatively and during follow-up

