### Participant timeline {13}

See Tables 1 and 2.

**Table 1 Tab1:** Standard participant timeline

Enrolment	Baseline	6-week follow-up	12-month follow-up	2-year follow-up	3-year follow-up	4-year follow-up	5-year follow-up
Informed consent	X						
EQ-5D-5L	X	X	X	X	X	X	X
SF-36	X	X	X	X	X	X	X
Medical history	X						
Physical examination	X	X	X	X	X	X	X
CT-angiography	X		X				
Duplex ultrasound	X	X	X	X	X	X	X

**Table 2 Tab2:** Modified participant timeline

Enrolment	Baseline	6-week follow-up	12-month follow-up	2-year follow-up	3-year follow-up	4-year follow-up	5-year follow-up
Informed consent	X						
EQ-5D-5L	X	X	X	X	X	X	X
SF-36	X	X	X	X	X	X	X
Medical history	X						
Physical examination	X	X					
CT-angiography	X		X				
Duplex ultrasound	X	X					
Telephone consultation		X	X	X	X	X	X

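### Secondary stent patency is assigned to repeated-measures ANOVA, which does not suit a censored yes/no endpoint, and the quality-of-life method is named in two different ways

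*Protocol article*

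**What the plan says.** The statistical methods section {20a} of the protocol article opens the secondary endpoints with a general rule: "Secondary endpoints will be analyzed by survival analysis techniques, such as Kaplan–Meier curve and log-rank tests". The next sentence reads: "ANOVA repeated measures will be used to estimate comparison QoL between the two groups, and secondary stent patency". Later sentences give the comparison of survival rates to the log-rank test, and diagnostic accuracy to logistic regression and ROC analysis.

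The section on non-adherence and missing data {20c} adds: "To handle missing data, mixed models without imputation will be performed". It does not say which outcomes this covers.

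The Outcomes section lists secondary stent patency and QoL among the secondary endpoints, "evaluated at 12 months and 5 years". The Follow-up section schedules a "quality of life (QoL) questionnaire at 6 weeks, 12 months, and then annually to 5 years postoperatively". Tables 1 and 2 mark EQ-5D-5L and SF-36 at baseline as well.

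**The concern.** There are two separate problems in one sentence.

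**Secondary patency.** At any moment a stent is either patent or not, and what matters over five years is whether and when patency is lost. Some patients will die, withdraw or stop having imaging before it is lost. ANOVA compares means of a continuous response and cannot represent a patient whose status is unknown after a certain date. An analyst who followed the sentence literally would have to code patency as 0/1 at each visit, and then drop or guess the visits without imaging. The preceding sentence points to a suitable method, so the plan gives two incompatible instructions for one endpoint.

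**QoL.** Here a method other than survival analysis is correct. The difficulty is that {20a} and {20c} name different methods for the same repeated scores. In its classical form, repeated-measures ANOVA needs a complete row for each patient; a likelihood-based mixed model does not. The choice decides who is in the comparison, and it bears on the intention-to-treat analysis promised in both sections.

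**Working it through.** **1. The plan's only related figure.** The Sample size section gives "alpha = 0.05, beta = 0.2, and power = 0.8" and rates of 85% and 60%. Two-sided, pooled variance, no continuity correction:

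- mean proportion = (0.85 + 0.60)/2 = 0.725
- 1.960 × √(2 × 0.725 × 0.275) = 1.960 × 0.6315 = 1.238
- 0.842 × √(0.85 × 0.15 + 0.60 × 0.40) = 0.842 × 0.6062 = 0.510
- n = (1.238 + 0.510)² / 0.25² ≈ 48.9, so 49 per arm and 98 in total

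This matches the plan (power at 49 per arm is 80.1%). It concerns the primary endpoint only, and nothing below alters it.

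**2. Secondary patency, sections side by side.**

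| Place | Method or data |
|---|---|
| {20a}, general sentence | Survival techniques for the secondary endpoints |
| {20a}, next sentence | Repeated-measures ANOVA for secondary patency |
| Outcomes | A secondary endpoint, assessed at 12 months and 5 years |
| Table 2 (modified timeline) | Duplex at baseline and 6 weeks only; CTA at baseline and 12 months only |

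Patients on the modified timeline have no tabulated imaging after 12 months. The Follow-up section lets CTA replace duplex at 1 year and beyond at the investigator's discretion, and suspected restenosis leads to CTA, so some later images may exist. They are not scheduled in Table 2. A complete-row ANOVA to 5 years would lose patients without later images; a survival analysis keeps each of them up to the last image.

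**3. QoL occasions.** Six follow-ups (6 weeks, 12 months, years 2, 3, 4 and 5) plus baseline make seven.

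**4. What classical ANOVA would cost, if it were used.** The document gives no rate of missed questionnaires. Assume a proportion m missed per visit, independent between visits, with baseline always complete. Expected complete cases = 98 × (1 − m)^k, where k = 6 for all follow-ups and k = 2 for 6 weeks and 12 months only.

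| m (assumed) | k = 2 | k = 6 |
|---|---|---|
| 5% | 98 × 0.903 = 88 | 98 × 0.735 = 72 |
| 10% | 98 × 0.810 = 79 | 98 × 0.531 = 52 |
| 15% | 98 × 0.723 = 71 | 98 × 0.377 = 37 |

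Over six visits the range widens to 87 at m = 2% and 26 at m = 20%. Misses that cluster in the same patients would leave more complete cases than shown; deaths would leave fewer. These figures show only why the choice between the two methods matters.

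**The case against.** The strongest defence is that {20a} and {20c} are compatible: a repeated-measures comparison is intended, and it is fitted as a mixed model when scores are missing. On that view the ANOVA phrase is loose wording and no patient is lost. For QoL this largely stands, and what remains is to make the two sections say the same thing.

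It is also fair to say that the survival sentence is a general rule followed by specific exceptions, as the ROC sentence shows. QoL scores cannot be analysed by Kaplan-Meier, so there is no survival contradiction for QoL.

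Neither argument rescues secondary patency. If the ANOVA sentence is a deliberate exception, it is an unsuitable one; if it is not, the two sentences conflict. Reading ANOVA as a mixed model for continuous scores does not help either, because the endpoint is binary.

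A reader might infer two stronger points, and the document supports neither:

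- That the plan discards every patient with one missed questionnaire. No section says so, and the mixed-model rule in {20c} would prevent it. Where assessment is limited to 12 months, only two follow-up questionnaires are involved.
- That baseline is analysed as one of seven outcome visits, so that a constant treatment difference shrinks to 6/7 of its size. The document does not say whether baseline is a response or a covariate, nor whether the group effect or the group-by-time interaction is tested. That detail may properly sit in an analysis plan.

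**Conclusion.** The point holds for secondary patency as written: the method named is unsuitable for a binary, time-dependent endpoint with censoring, and it contradicts the sentence before it. This rests on reading patency as patent/not patent, which fits the dichotomous <50% stenosis criterion given for primary patency.

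For QoL the point is narrower: two sections name two methods for the same data and should be reconciled. Any loss of patients is conditional on classical ANOVA over several visits and on missingness rates that the document does not give, so no size can be attached to it.

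The error is confined to secondary endpoints. It should be corrected before analysis, but it does not touch the primary comparison or the 98 patients.

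**What to change.** - **Secondary patency.** Delete the ANOVA assignment. State: Kaplan-Meier curves by randomised arm with a log-rank test, estimates at 12 months and 5 years, and patients without loss of patency censored at their last imaging. Say how death before loss of patency is treated. Censoring is the default and needs to be a stated choice, since the endpoint list already includes overall survival.
- **QoL.** Replace the ANOVA wording in {20a} with a mixed model for repeated measures that uses all available post-baseline visits and adjusts for the baseline score already collected. Name QoL explicitly in {20c} so that the two sections agree. The covariance structure and the contrast of main interest can be left to the analysis plan. A mixed model does not by itself settle how scores after death are regarded, so one sentence on that is useful.

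The cost is a few sentences. No new data, visits or patients are needed, and standard software suffices.
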